## Abstract

The loss of an infant during the perinatal period has been recognized as a complex and potentially traumatic life event and can have a significant impact on women’s mental health. However, often times, psychological aftercare is typically not offered, and manualized interventions are rarely used in clinical care practice and have seldom been evaluated. In recent years, a growing number of studies have demonstrated the efficacy of virtual reality (VR) interventions to facilitate the expression and coping with emotions linked to a traumatic event. The objective of the proposed paper is to present the protocol of a randomized control trial aimed to assess a novel VR-based intervention for mothers who experienced a perinatal loss. We hypothesize that the VR-based intervention group will show significantly reduced symptoms related to grief, postnatal depression and general psychopathology after treatment relative to a treatment-as-usual (TAU) group. Participants would be randomly assigned to the TAU + VR or to the VR + TAU condition. The TAU condition as well as the VR-based intervention will last 3 weeks, after which women will complete a post-assessment. The proposed VR-based intervention will consist in three weekly sessions focused, respectively on: (1) collect information about the loss and psychoeducation about perinatal grief, and introduction to the virtual environment; (2) through the use of the virtual environment, women will be assisted in the elaboration and acceptation of loss; (3) recreate, using the specific features of the virtual environment a positive metaphor representing woman’s future life. VR has proved to be a valid intervention tool in clinical psychology, and in the last years VR technologies have become more affordable to be used in clinical practice. With the present study we propose to answer to the unquestionable need for interventions addressed to ameliorate the emotional effects in women who experienced perinatal loss, by exploiting also the therapeutic opportunities offered by a new technology as VR.

## Introduction

The perinatal period is a complex time in women’s lives. It is a transitional time which requires important changes and challenges as searching for a new identity as an individual, a partner in a couple, and a member of a society (Bibring, 1959; Barclay et al., 1997). The complexity of this period can dramatically increase if women experience perinatal loss. The loss of an infant during the perinatal period has been recognized as complex emotional experience and a potentially traumatic life event for women who experienced it, no matter how and at what gestational stage it occurred (e.g., Berman, 2001; Klier et al., 2002; Bennett et al., 2012). Indeed, although mothers have few or no direct life experiences with their infant, grief in a context of the loss of a child in the perinatal period does not vary significantly in terms of intensity from other type of loss (Kersting and Wagner, 2012). In this paper we use the term perinatal loss to refer to the experiences of women who lost a child during the perinatal period (i.e., loss due to miscarriage, stillbirth, termination due to medical indications, and neonatal death). Miscarriage, stillbirth, and neonatal death continue to be significant topics of concern in the twenty-first century. In Québec (a province of Canada) it is estimated that each year 20,000 pregnancies do not terminate in a live birth (Agence de la santé publique du Canada, 2008).

Research and clinical reports have shown that the loss of a child can cause a multitude of emotions and psychological distress in many women (de Montigny et al., 2017b). Grief is a natural, non-pathological phenomenon and a deeply personal process (Kersting and Wagner, 2012). Reactions to the loss of a significant one can involve transient impairment of daily functioning, elusion of social activities, presence of recurrent and intrusive thoughts, feelings of deep longing and incapability of feeling sensations and emotions (Kersting and Wagner, 2012). The severity of psychological distress generally tends to wane over the first year after the loss (e.g., Bennett et al., 2012). Nonetheless about 20% of women continue to suffer from clinically significant symptoms 1 year after their loss (Boyle et al., 1996; Leon, 2001). Perinatal losses have been shown to have detrimental effects on both mothers’ and fathers’ psychological well-being, on the other members of their families, and are also associated with post-traumatic stress, depression, anxiety, and sleep disturbances (Boyle et al., 1996; Hughes and Riches, 2003). Hughes et al. (2002) reported that approximately 20% of women who experienced a perinatal loss can manifest depression or posttraumatic stress symptomatology. Furthermore, losing a child during the perinatal period has been identified as a complex and potential threatful life experience, which can, in some cases, further develop in complicated grief reactions, characterized by more disruptive, pervasive, or stable symptoms than in a normal grief response. Persistent complex bereavement disorder, also known as complicated grief disorder, has been included in the Diagnostic and Statistical Manual of Mental Disorders, 5th Edition (DSM-5; American Psychiatric Association, 2013).

Despite the increasing recognition that perinatal loss can lead to significant consequences on women’s mental health, often times, few of the women affected receive emotional and psychological support (de Montigny et al., 2017b). The necessity of psychological interventions supporting women after a pregnancy loss is unquestioned in the scientific literature. Nevertheless, psychological aftercare is typically not offered, and manualized interventions are hardly applied in clinical care practice (e.g., Kersting and Wagner, 2012; de Montigny et al., 2017b). The lack of manualized interventions mirrors the corresponding lack in the scientific literature. Indeed, in an attempt to systematically review the scientific literature for psychological and support interventions to reduce levels of stress, anxiety or depression on women who experienced a miscarriage, Campillo et al. (2017) did not find any randomized controlled trials.

In recent years, new technologies have been increasingly used for the assessment, treatment and better understanding of mental health related problems. For instance, Internet- and computer-based interventions are increasingly popular, ranging from pure psychoeducation websites to online self-help groups, self-help interventions, counseling, and even psychotherapy for all sorts of mental health problems (e.g., Andersson and Titov, 2014; Ebert et al., 2018; Moshe et al., 2020), including for parents who experiences perinatal loss (e.g., Kersting et al., 2011a, b). Virtual reality (VR) is another technology that saw an exponential increasing in its popularity in clinical and health psychology. VR embodied the unique opportunity to create (and recreate) simulated environments “where the testing, training, teaching, and treatment of cognitive, emotional, and sensorimotor processes can take place under stimulus conditions that are not easily deliverable and controllable in the physical world” (Rizzo and Bouchard, 2019, p. 6). More specifically, numerous studies have demonstrated the efficacy of VR-based interventions to facilitate the expression and coping with emotions (e.g., Rizzo and Bouchard, 2019). Most of the virtual environments created and used as toll to treat potentially traumatic events are realistic in the sense that their aim is to virtually replicate, in a safe and controlled situation, a real life aversive situation (e.g., war environments, Peskin et al., 2019; sexual assault, Loranger and Bouchard, 2017). The virtual environment “EMMA World” was developed as a tool to facilitate the expression and coping with emotions in stress-related disorders (posttraumatic stress disorder, complicated grief, and adjustment disorders) (Baños et al., 2009, 2011). EMMA’s World objective is not to realistically reproduce the physical features of a threatening or traumatic event, but rather to employ symbols and personalized elements that can evoke emotional reactions and can facilitate the expression of patients’ emotional state in a symbolic way that will be used by the therapist. To achieve therapeutic objectives, different virtual landscapes and symbols are customized to be personally meaningful for the patient; those virtual elements are used to recreate, in a safe and controlled environment, emotions and situations that are difficult for the person to confront and process (Baños et al., 2011). The possibility to use personalized stimuli in EMMA World could be particularly relevant to support women in coping with their perinatal loss and the multitude of emotions that they can experience in this critical period of their life. It is expected that such a focus intervention would be more effective than services routinely provided and referred-to as treatment-as-usual (TAU).

The objective of the proposed paper is to describe the protocol of a randomized control trial aimed to assess a VR-based intervention for mothers who are experiencing perinatal loss. We hypothesize that: (a) when administered before TAU, the VR-based intervention will lead to a greater reduction in symptoms related to grief, postnatal depression and general psychopathology, compared to participants receiving TAU; (b) when administered after TAU, the participants will show a significant pre/post-VR-based intervention improvement in symptoms related to grief, postnatal depression and general psychopathology.

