## Materials and Methods

### Inclusion/Exclusion Criteria

The intervention program will be offered to mothers who had recently experienced a perinatal death, including: having lost a child during pregnancy because of miscarriage (i.e., embryo or fetus death prior the 28th week of gestation); termination due to medical indications; stillbirth (i.e., fetus death after 28 completed weeks of gestation); or neonatal death (i.e., infant death within the first 7 days of life). Women who have experienced perinatal death while pregnant within no more than 1 year before the enrollment will be invited to participate to the study. Exclusion criteria include significant vision impairments despite wearing corrective glasses or lenses, presence of a diagnosed mental disorder, and being under psychological treatment. The target sample will be composed of 40 women. To evaluate the size of the involved samples, we used a Sample Size Calculation (Power Analysis) using the software GPower^∗^3. We based the power-analysis on a recent study assessing efficacy of an EMMA’s World-based intervention for the treatment of stress-related disorders. We estimated a minimum of 40 women to be included in the trial, in order to achieve a minimum power of 90%, considering a medium effect size of *f* = 0.25, and a significance level of 0.05.

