#### Outcome Measures

Perinatal grief will be measured with the Perinatal Grief Scale (PGS; Potvin et al., 1989; Toedter et al., 2001; French validation: Paris et al., 2017). The PGS is composed by 33 statements divided into three subscales: Active Grief, which includes 11 items that refers to the normal emotional reactions to the loss (i.e., sorrow, missing the child, or crying); Difficulty Coping, which includes 11 items that refers to more complex emotional reactions (e.g., difficulty with normal life activities, lack of support, problems in marital relationships); and Despair, which refers to long-term effects of the loss (e.g., existential feelings of helplessness and hopelessness) and relevant coping strategies. The PGS uses a Likert type scale with five response options ranging from 1 (i.e., “strongly disagree”) to 5 (i.e., “strongly agree”). The total score varies between 33 and 165 points, with values above 91 points represent potential psychiatric morbidity. Complicated grief will be measured with the Inventory of Complicated Grief (IDC; Prigerson et al., 1995; French adaptation: Zech, 2006). This instrument consists of 19 items concerning the immediate bereavement-related thoughts and behaviors of the respondent, who is asked to report the frequency (from “0 = never” to “4 = always”) with which he/she currently underwent each of the emotional, cognitive, and behavioral states detailed in the instrument. Individuals with an ICG total scores > 25 reported to have significantly worse general, mental and physical health, social functioning, and bodily pain, as well as depression. Thus, the authors concluded that this score should be the criterion for distinguishing between uncomplicated and complicated grief reactions. Depressed mood will be assessed using the Beck Depression Inventory-II (BDI-II; Beck et al., 1996; Validated in French by Édition du centre de psychologie appliquée, 1996). The BDI-II is one of the most widely used instruments to assess depressive symptoms and their severity following the criteria of the Diagnostic and Statistical Manual of Mental Disorders (DSM-IV; American Psychiatric Association, 2000). The BDI-II consists in 21 symptoms assessed with multiple-choice responses rated on a scale value of 0–3. The maximum total score is 63, with the following standardized cutoffs: 0–13: associated to normal minimal range, 14–19: associated to mild depression, 20–28: associated to moderate depression, and 29–63: associated to severe depression. Postnatal depression will be assessed through the 10-item Edinburgh Postnatal Depression Scale (EDPE; Cox et al., 1987). The EPDS is the most commonly used screening tool to determine women’s clinically significant signs of depression during the perinatal period (e.g., McCabe-Beane et al., 2016). Since many symptoms of depression overlap with normal states in women during the perinatal period (e.g., sleep disturbance), EPDS items were planned to evaluate only the mood components of depressive symptoms. The 10 items are rated on a scale from 0 to 3, and are reflecting the mood during in the last 7 days. EPDS score of 10 and 13 are proposed as cut-off scores indicative of potential minor or major depression, respectively (Cox et al., 1987; see McCabe-Beane et al., 2016 for other cut-off scores). Anxiety will be assessed using the State and Trait Anxiety Inventory-form Y (STAI-Y; Spielberger, 1983; French validation: Gauthier and Bouchard, 1993). It consists of a self-report instrument conceived to evaluate trait (a stable personality trait) and state (a temporary and fluctuating condition) anxiety. The STAI-Y consists of two subscales (trait and state anxiety) with 20 items each rated on a 4-point scale. Higher scores indicate greater anxiety. Affect will be measured with the Positive and Negative Affect Scale (PANAS; Watson et al., 1988; French validation: Gaudreau et al., 2006). The PANAS is a widely used scale which consists of two subscales, one measuring positive affect and the other assessing negative affect. Each subscale is composed of 10 items, scored on a 5-point Likert scale ranging from 1 (i.e., “very slightly or not at all”) to 5 (i.e., “extremely”). Clinical global impression assessed by the therapist will be assessed at pretest and post-test using the Clinical Global Impression rated by the therapist (CGI; Guy, 1976). It consists in a 3-item observer-rated scale that measures illness severity (CGIS), global improvement or change (CGIC) and therapeutic response. The CGI is rated on a 7-point scale, with the CGIS characterized by a range of responses from 1 (i.e., “normal”) to 7 (i.e., “amongst the most severely ill patients”). CGI-C scores range from 1 (i.e., “very much improved”) to 7 (i.e., “very much worse”). Treatment response ratings should consider both treatment-related negative events and therapeutic efficacy, ranging from 0 (i.e., “marked improvement and no side-effects”) to 4 (i.e., “unchanged or worse and side-effects outweigh the therapeutic effects”). Each CGI’s component is rated separately, and this instrument does not provide a global score.

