
#### Satisfaction With the Intervention

Women’s satisfaction with the intervention will be rated at post-test using the Client Satisfaction Questionnaire (CSQ-8; Attkisson and Zwick, 1982). The CSQ-8 is a self-report measure designed to assess clients’ satisfaction with mental health services. The 8-items versions has eight question-items (quality of service, kind of service, met needs, recommend to a friend, amount of help, deal with problems, overall satisfaction, and come back), rated using a 4-point Likert scale, with a possible total scores can vary from 8 to 32. Higher scores indicate greater satisfaction with the service.

In order to test our hypothesis, we will perform repeated measures (Mixed Model) ANOVA with 3 Times (Pre, Post-test 1, Post-test 2) and 2 Conditions (VR-based intervention first, followed by TAU, i.e., VR+TAU; TAU first, followed by VR-based intervention, i.e., TAU+VR). For ethical reasons, the study is a randomized control crossover design, where all participants receive an intervention. The Pretest to Post-test 1 allows the comparison of VR-based treatment versus TAU, and the Post-test 1 to Post-test 2 allows to test the added value of the VR-Based intervention to TAU.

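### No primary outcome or success rule is named for hypotheses spanning three symptom domains and about nine scores, so the main claim has no defined error rate and the sample size is tied to no endpoint

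*Protocol article*

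**What the plan says.** The Introduction closes with two hypotheses. Hypothesis (a) is the randomised one: VR given first should produce "a greater reduction in symptoms related to grief, postnatal depression and general psychopathology, compared to participants receiving TAU". Hypothesis (b) predicts improvement in the same three domains from before to after VR in women who had TAU first. No domain is ranked.

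Outcome Measures describes, under one heading:
- PGS (a total and three subscales)
- ICG
- BDI-II, assigned to depressed mood
- EPDS, assigned to postnatal depression
- STAI-Y state and trait
- PANAS positive and negative affect
- three CGI components, rated separately with no global score

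None is labelled primary or secondary, and none is identified as the measure of general psychopathology. The list is not sorted by purpose either: it includes an inventory "conceived to evaluate trait (a stable personality trait) and state (a temporary and fluctuating condition) anxiety", with both parts presented as outcomes.

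The analysis paragraph, printed under Satisfaction With the Intervention, gives one generic model, "repeated measures (Mixed Model) ANOVA with 3 Times (Pre, Post-test 1, Post-test 2) and 2 Conditions". It names no score, no significance level and no rule for combining results. The sample-size statement under Inclusion/Exclusion Criteria says "The target sample will be composed of 40 women", "considering a medium effect size of *f* = 0.25" and "a significance level of 0.05", again without naming an outcome.

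**The concern.** A reader of the final report could not tell from this protocol which result decides hypothesis (a). If VR beat TAU on one affect scale and on nothing else, the text would neither allow nor exclude calling the hypothesis supported. Two consequences follow.

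- **Error rate.** Without a primary outcome or a success rule, no type I error rate attaches to the main claim. How high it could be depends on how many scores are tested and what counts as success.
- **Power.** The claim of at least 90% power attaches to no endpoint. An effect of f = 0.25 cannot be judged plausible, or converted to points on a scale, until a score is named.

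The open meaning of general psychopathology adds to this: BDI-II, STAI-Y, PANAS or CGI could each be put forward as its measure after the results are known.

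**Working it through.** **1. The plan's own figure.** The inputs are f = 0.25, alpha 0.05, power 90%, two conditions and three times. The within-subject correlation (rho) and the sphericity factor (epsilon) are not stated, and 1:1 allocation is assumed. For the condition-by-time interaction, lambda = f² × N × m × epsilon / (1 − rho).
- With rho = 0.5, epsilon = 1, m = 3 and N = 40: lambda = 0.0625 × 40 × 3 / 0.5 = 15, on 2 and 76 degrees of freedom. Power is 93.5%, and N = 36 suffices for 90%.
- N = 40 is exactly the requirement at rho = 0.45, epsilon = 1 (power 91.0%), or at rho = 0.5, epsilon = 0.9 (91.5%).

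So 40 is attainable for one test on one score. The stated inputs do not fix it uniquely, and it is not disputed here.

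**2. Counting scores.** PGS total, ICG, BDI-II, EPDS, STAI state, STAI trait, PANAS positive, PANAS negative and CGI severity make nine. All three CGI components give 11, and adding the PGS subscales gives 14. The CGI is described only as assessed at pretest and post-test, so its place at all three times is unclear. Leaving it out gives eight, and leaving out trait anxiety as well gives seven.

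**3. Chance of at least one false difference under hypothesis (a).** This assumes no true effect, each of k scores tested unadjusted at two-sided 0.05, and any one counted.
- Independent scores, either direction: 1 − 0.95^9 = 1 − 0.630 = 37.0%.
- Independent scores, VR's favour only: 1 − 0.975^9 = 20.4%.
- Equicorrelated test statistics with correlation r and c = 1.96: 1 − ∫ φ(x) [Φ((c − √r x)/√(1 − r)) − Φ((−c − √r x)/√(1 − r))]^k dx. The second Φ term is dropped for VR's favour only.

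The documents give no correlation between scores, so r is an assumption shown as a range. Each cell reads either direction / VR's favour.

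| Scores | r = 0 | r = 0.5 | r = 0.7 |
|---|---|---|---|
| 3 (one per domain) | 14.3% / 7.3% | 12.5% / 6.3% | 10.9% / 5.5% |
| 7 | 30.2% / 16.2% | 23.0% / 11.5% | 17.8% / 8.9% |
| 8 | 33.7% / 18.3% | 25.0% / 12.5% | 19.1% / 9.5% |
| 9 | 37.0% / 20.4% | 26.9% / 13.5% | 20.2% / 10.1% |
| 11 | 43.1% / 24.3% | 30.4% / 15.2% | 22.3% / 11.1% |

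At r = 0.8 the nine-score figures are 16.5% / 8.3%. The nominal values for one test are 5% / 2.5%.

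**4. Check against the planned test.** Simulating nine 2-df interaction F-tests with 40 women gave 36.3% at r = 0, 27.5% at 0.5 and 21.4% at 0.7, close to the normal-theory values. An omnibus 2-df test has no direction, so the VR's-favour figures refer to a single contrast such as the Pre to Post-test 1 change.

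**5. Cost of correcting over many scores instead** (rho = 0.5, three times).
- Bonferroni over nine (0.05/9 = 0.0056): power at N = 40 falls from 93.5% to 74.7%, and 54 women are needed for 90%.
- Bonferroni over three domain scores (0.05/3 = 0.0167): 85.6%, and 46 women.

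**The case against.** The strongest reply is that the large percentages rest on a decision rule the protocol never states, and much of this stands.

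- **Testing each score at 0.05 is an inference.** That level appears only as a power input. The analysis paragraph gives none, and a multiplicity rule is commonly left to an analysis plan, which is not shown here. Its absence is therefore not the finding.
- **Any one significant score being enough is also an inference.** The hypothesis joins its three domains with a conjunction. If all three had to be significant, the false-claim rate could not exceed that of a single test, 5%. But the protocol does not state that rule, and the sample size is not stated to be for it: with 93.5% power on each of three independent scores, joint power would be 0.935³ = 82%.
- **A reader might take 20-37% as the chance of wrongly concluding that VR works.** It counts false differences in both directions. In VR's favour it is about half that.
- **A reader might carry the figures over to hypothesis (b).** They do not carry over. That is an uncontrolled change within one arm, and the Introduction says distress generally wanes over the first year after the loss. The risk of crediting VR wrongly there is not set by this formula.
- **The 37% end needs independent scores.** That is unlikely for grief, depression and anxiety scales completed by the same women.

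Nothing in the documents shows that the investigators intend to report selectively, and that is not claimed.

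What the reply does not remove is the missing primary outcome. That choice defines the trial's question and its sample size, so it belongs in the protocol. The article presents hypotheses, outcomes, a power calculation and a model without singling out a score. A later multiplicity rule would still leave the power statement without an endpoint.

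**Conclusion.** The point holds in this form. The protocol fixes no primary outcome and no success rule for three unranked domains measured by about nine scores. It maps general psychopathology to no scale, and it ties its only alpha and effect size to none of them.

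The size is conditional. With nine scores, unadjusted two-sided tests at 0.05 and any one accepted as support, the chance of at least one false difference under hypothesis (a) is about 20-37% in either direction, or about 10-20% in VR's favour against 2.5% nominal. This rests on equal correlations between 0.7 and 0, which the documents do not give. With one score per domain it would be about 11-14% in either direction. The documents do not support stating any of these as the trial's actual error rate, or applying them to hypothesis (b). Nor do they show that 40 women is a wrong number.

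**What to change.** Before outcome data are seen, amend the protocol as follows.

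1. Declare one primary score and time point, tested at two-sided 0.05. PGS total at Post-test 1 is a reasonable example: it is specific to perinatal loss, and Post-test 1 closes the randomised comparison before crossover.
2. Tie the sample-size statement to that score and contrast, giving the expected difference, the within-subject correlation and the test.
3. State which scale represents general psychopathology. The investigators must choose. BDI-II is not an obvious default, because Outcome Measures assigns it to depressed mood.
4. Test the other domain measures, such as ICG, EPDS and the scale chosen in step 3, as secondary outcomes with Holm correction.
5. Report the remaining scores, and hypothesis (b), as supportive estimates with 95% confidence intervals.

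The cost is wording, and fewer scales can be claimed as significant. Step 2 may also show that 40 is slightly short or ample. For a two-time interaction with f = 0.25 and rho = 0.5, lambda = 0.0625 × 40 × 2 / 0.5 = 10, power is 86.9% and 46 women are needed for 90%. At rho = 0.6, 36 suffice. A single primary outcome avoids the 54 women that Bonferroni over nine scores would need under the three-time assumptions above.

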**FIGURE 3 F3:**
[figure not shown]
CONSORT flowchart for the proposed clinical trial: adapted from Consort 2010.

Women will be randomly assigned to the VR+TAU or to the TAU + VR condition. Randomization will be performed using a true random number service^2^, and will be not stratified based on participant’s characteristics. The TAU condition is a homogenous standard program proposed by the CERIF at UQO based on group counseling offered to women and men who experienced a perinatal loss. The TAU condition as well as the VR-based intervention will last 3 weeks, after which women will complete a post-assessment (see Figure 3). The VR-based intervention will be conducted at the Cyberpsychology Laboratory of UQO; the TAU group counseling will take place at the CERIF of UQO.

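### Hypothesis (b) names no comparator, so a pre/post change in the TAU+VR arm cannot show the added value of VR over natural recovery or delayed TAU benefit

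*Protocol article*

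**What the plan says.** The last paragraph of the Introduction states two hypotheses. Hypothesis (a) has a comparator: "the VR-based intervention will lead to a greater reduction in symptoms related to grief, postnatal depression and general psychopathology, compared to participants receiving TAU". Hypothesis (b) has none: "when administered after TAU, the participants will show a significant pre/post-VR-based intervention improvement in symptoms related to grief", and likewise for postnatal depression and general psychopathology.

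The analysis paragraph, at the end of the section Satisfaction With the Intervention, plans a "repeated measures (Mixed Model) ANOVA with 3 Times (Pre, Post-test 1, Post-test 2) and 2 Conditions". It gives each interval a meaning. For the first, "The Pretest to Post-test 1 allows the comparison of VR-based treatment versus TAU". For the second, "the Post-test 1 to Post-test 2 allows to test the added value of the VR-Based intervention to TAU".

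Three other statements bear on this:
- Introduction, on the natural course: "The severity of psychological distress generally tends to wane over the first year after the loss".
- Inclusion/Exclusion Criteria, on who is invited: "Women who have experienced perinatal death while pregnant within no more than 1 year before the enrollment".
- Procedure, on duration: "The TAU condition as well as the VR-based intervention will last 3 weeks", with an assessment after each. No gap between the two treatments is described.

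**The concern.** Hypothesis (b), taken as written, is met when the TAU+VR arm improves between Post-test 1 and Post-test 2. Two things other than VR push scores the same way over those weeks. One is the natural decline in distress that the protocol describes. The other is late benefit from the group counselling that these women have just finished. A change within one arm contains both of them plus any VR effect, and nothing in that arm's data can divide the sum.

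This matters because (b) is one of only two stated hypotheses and the article attaches a causal reading to it. A significant result could be presented as evidence that VR adds something to usual care when it shows only that time has passed.

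**Working it through.** **1. The two hypotheses side by side.** Hypothesis (a) is a difference between randomised arms over the same weeks, so a time trend common to both arms cancels. Hypothesis (b) is a difference between two time points in one arm, so the trend stays in. Write the expected second-period change in TAU+VR as V + T + L, where V is the VR effect, T the natural trend and L the late TAU effect. The pre/post test asks whether V + T + L differs from zero, but the stated interpretation concerns V alone.

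**2. How often the test would be significant with V = 0.** The protocol gives no figure to reproduce here, so the following are assumptions:
- n = 20 in the TAU+VR arm (half of the target of 40; the allocation ratio is not stated);
- a paired t-test at two-sided 0.05, critical value t(0.975; 19) = 2.093;
- within-person correlation ρ of 0.5, 0.7 or 0.8;
- a natural fall of d SD in the 3 weeks, with no late TAU effect.

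The SD of the change, in units of the outcome SD, is √(2(1−ρ)): 1.000, 0.775 and 0.632. The noncentrality is d·√20 / √(2(1−ρ)). For d = 0.2 and ρ = 0.5 this is 0.2 × 4.472 / 1.000 = 0.894, and the noncentral t with 19 degrees of freedom exceeds 2.093 with probability 0.133.

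Chance of a significant improvement (2.5% nominal in that direction):

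| Drift d | ρ = 0.5 | ρ = 0.7 | ρ = 0.8 |
|---|---|---|---|
| 0.1 SD | 6% | 8% | 10% |
| 0.2 SD | 13% | 19% | 27% |
| 0.3 SD | 25% | 38% | 52% |
| 0.4 SD | 40% | 59% | 77% |

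Simulation with 20,000 trials per setting agrees: 6.3% and 7.7% at d = 0.1, 13.4% and 19.5% at d = 0.2, 24.2% and 37.5% at d = 0.3 (ρ = 0.5 and 0.7).

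**3. Which drifts are credible.** The protocol says only that distress falls over the first year. If the fall were linear, 0.1 SD per 3 weeks would be 0.1 × 52/3 ≈ 1.7 SD over the year, and 0.2 to 0.4 SD would be about 3.5 to 7 SD. The higher rows therefore need a decline concentrated in the early weeks and women enrolled during them. The 0.1 SD row is the easier one to defend as an average.

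**4. The controlled alternative.** Take the Post-test 1 to Post-test 2 change in TAU+VR minus the same change in VR+TAU, as a two-sample t-test with 20 per arm. In the same simulations, with a common drift of 0 to 0.3 SD per period, its two-sided error rate was 4.8-5.2%. For a true difference in change of 0.5 SD the noncentrality is 0.5·√10 / √(2(1−ρ)) = 1.58, 2.04 and 2.50, which gives power of 34%, 51% and 68%.

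**The case against.** The strongest reply is that the planned ANOVA has two conditions. The VR+TAU arm is measured at Post-test 1 and Post-test 2 as well, so the Time by Condition term contains a randomised second-period contrast, and the sentence on added value directly follows the description of that model. This stands in part. It would be wrong to infer that the trial has no concurrent data in the second period. But (b) does not refer to the other arm, and no sentence says that the second-period change is compared between arms. Follow-up contrasts may be left to an unseen analysis plan. The hypothesis itself is fixed here, and a plan that implemented it faithfully would run an uncontrolled test.

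The article also names no paired t-test and no decision rule for (b). The figures above therefore illustrate the pre/post wording; they do not describe a stated test.

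Two stronger readings are tempting, and the protocol supports neither:
- A reader might infer that a significant result for (b) is likely even if VR does nothing. That needs a rate above 50%, which occurs only at 0.3 SD with ρ = 0.8 and at 0.4 SD with ρ = 0.7 or 0.8. Nothing in the protocol shows that such drifts are typical.
- A reader might add regression to the mean. The eligibility criteria set no minimum symptom score, and (b) starts at Post-test 1, not at screening, so there is no stated selection on a high value.

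Finally, the Abstract and Discussion restate only the between-group hypothesis. That is reassuring about the main claim, and (a) is unaffected by this point.

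**Conclusion.** The point holds as a flaw in how (b) is defined and interpreted. A within-arm change after TAU cannot be read as the added value of VR, whatever the rate of natural recovery. That conclusion needs no assumed numbers.

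The size does need them. The error in the favourable direction rises from 2.5% to 6-10% under a modest drift of 0.1 SD, and to 13-27% or 25-52% if women improve by 0.2 or 0.3 SD in three weeks. Late TAU benefit would add to this and cannot be sized from the protocol. The sample size of 40 has no bearing on the point.

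**What to change.** Remove the added-value reading of the within-arm change. Then do one of the following:
- keep (b) as a descriptive summary of change in the TAU+VR arm, with no efficacy claim; or
- restate (b) as the difference between arms in Post-test 1 to Post-test 2 change (TAU+VR minus VR+TAU), with a 95% CI, labelled supportive.

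If the second option is taken, state its limits. It compares VR after TAU with TAU after VR. The VR+TAU arm carries over its first-period effect and may have less room to improve. Power is about 34-68% for a 0.5 SD difference in change, so a non-significant result would say little.

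In either case, say that conclusions about efficacy rest on the randomised Pretest to Post-test 1 comparison in hypothesis (a).

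The cost is a rewording and, at most, one contrast from data already planned. No participants, visits or measures are added. The trial gives up one claim that its design cannot support.
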